### Onboarding Procedure

Recruitment materials will direct participants to Apple or Android app stores. Once the app is downloaded, potential participants will be directed to review the plain language statement, as well as the terms of use and privacy policy. During this process, potential participants will also be asked to provide informed consent by confirming that they meet the eligibility criteria and are willing to participate in the trial activities (completion of brief surveys, EMAs, and ecological momentary interventions). Participants are advised during the consent process that, during the trial period, the app will present strategies specifically aligned with EMA responses with varying levels of detail. Those who provide consent will create an account for the *Cogniss* platform, including setting a username and password and providing an email address. Following account creation, participants will be required to read a brief app description and information about how the app works. Participants will then be directed to the preintervention survey (including their mobile number, interest in being contacted for further research, and interest in participating in the optional semistructured interview), after which they will be encouraged to complete an EMA.

### Distal and Proximal Outcomes

The *distal outcome* for *Gambling Habit Hacker* is gambling expenditure. The *primary proximal outcome* is goal adherence (operationalized as a binary outcome, with success defined as actual gambling expenditure being no greater than 10% higher than planned gambling expenditure). In exploratory analyses, the impact of altering the flexibility percentage (eg, 20% flexibility) and continuously scaled measures of adherence may also be explored. To specify expenditure goals over the 28-day MRT, participants are required to indicate their intended gambling episodes and associated expenditure during preintervention measurement using a TimeLine Follow-Forward [58]. Actual expenditure will be collated via the event record in each EMA: S*ince the last time you checked in, how much have you spent in $ gambling? Record 0 if you have not gambled*. *Secondary proximal outcomes* are drawn from EMA data, which allows us to examine changes across the course of the intervention. Outcomes include the strength of intention to adhere to gambling goals, goal self-efficacy, and urge self-efficacy, all of which are measured in the subsequent EMA (see the *Tailoring Variables* section for information on the source and description of each variable).

### Decision Points

Participants will take part in a 28-day MRT in which *Gambling Habit Hacker* will administer an EMA protocol that uses time-based sampling that incorporates event-based sampling. Each EMA comprises 18 items that assess influential internal or situational cues and an item that assesses an event record of any gambling expenditure since the previous EMA. The EMA is an active assessment that is undertaken in-app and by self-report, with completion prompted by push notifications delivered to participants at random times during 3 prespecified times during a day: morning (8:30 AM-11:00 AM), afternoon (1:00 PM-3:30 PM), and evening (5:30 PM-8:00 PM). EMA can be auto-launched via notification or through the app. Each EMA takes approximately 2 minutes to complete and is most often measured on a 5-point Likert-type scale with varying response options. In the case where participants are not able to complete the EMA when the push notification is delivered, they will be able to complete the EMA up to two hours after receiving the push notification to accommodate possible unavailability such as driving or working [55,59]. If the EMA is not completed within 2 hours of receiving the push notification, it is no longer accessible and is considered *not completed*.

To enhance EMA compliance at the outset and during the delivery of the intervention, the following contact protocol will be adopted: (1) an automated welcome email when registering, (2) a reminder email to participants who fail to complete onboarding or fail to complete an EMA for >48 hours following onboarding, and (3) a reminder telephone call by qualitatively or clinically trained research fellows who still fail to complete onboarding or an EMA in the subsequent 48-hour period (with a follow-up SMS text message, if no answer or second follow-up email, if they provided no valid phone number). Participants who fail to complete an EMA following this protocol will receive no further contact but will be eligible to receive follow-up evaluations, as long as they complete onboarding, at least one EMA, and have some engagement with the app interventions.

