### Within-Group Evaluation

In addition to MRT, this study will include a within-group follow-up evaluation over a 6-month period to (1) examine within-group change over the 6 months following the end of the MRT and (2) identify predictors of these longer-term treatment outcomes (including usage of the app over the follow-up period). Surveys taking 10 to 15 minutes will be administered before intervention (via the app), as well as after intervention and at the 6-month follow-up (via Qualtrics). Descriptive and covariate measures will include sociodemographic characteristics (age, sex, current residence, primary ethnicity, and personal annual gross income), problem gambling activities (6 types of gambling), and intended gambling behavior as measured by the TimeLine Follow-Forward [58], volitional phase [72], and help seeking [73]. To assess the volitional phase, participants will be presented with 4 statements: I am deciding whether I need to change my gambling (predecisional); I am getting ready to change my gambling (postdecisional); I have already started to change my gambling (actional); and I have successfully changed my gambling and want to maintain this change (postactional). Posttrial and 6-month follow-up participants will be asked to report on their previous help-seeking behavior using 9 items from the Help-Seeking Questionnaire [73]. This includes 5 items related to high-intensity help seeking and 3 items related to low-intensity help seeking. An item related to self-directed help seeking will also be administered to assess engagement with self-exclusion.

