The primary outcome for the within-group evaluation will be gambling expenditure (measured using a TimeLine Follow-Back at the preintervention evaluation, the EMA data collected during the intervention period and amalgamated for the posttreatment evaluation, and single items at the 6-month evaluation). Secondary outcomes will include gambling symptom severity measured using the G-SAS [57], gambling frequency with the TimeLine Follow-Back at the preintervention evaluation (EMA data at the posttreatment evaluation and single items at the 6-month evaluation) [74], psychological distress measured using the Kessler 6 Psychological Distress Scale [75], personal well-being measured using the Personal Wellbeing Index [76], the Brief Situational Confidence Questionnaire [77], and planning propensity measured using an adapted action control questionnaire that assesses action planning, coping planning, and action control [78]. A summary of the measures and the measurement time points (before intervention, after intervention, and follow-up) for the within-group evaluation are presented in Multimedia Appendix 2.

To enhance engagement with the posttreatment and 6-month follow-up evaluations, the following protocols will be implemented. An email will be sent to all participants to prompt survey completion, with a second reminder email for those who fail to complete within a week. An advance notice email will also be sent a week before the 6-month surveys are administered. For those who have not completed the survey after a further week, up to two reminder telephone calls will be made by a clinical or qualitatively trained researcher. At each time point, the option to complete the survey over the phone with a trained research fellow will be offered. Participants who do not complete posttreatment evaluation will be contacted at the 6-month evaluation unless they have withdrawn from the study.

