### Statistical Analyses

To assess the research questions, the method of generalized estimating equations will be used, with an appropriate link function for the outcome of interest (eg, logit or identity). Although an exchangeable working correlational structure is intended to be used for the analyses, considerations will be given to alternative correlational structures based on the observed within-person correlation pattern over the course of the study (eg, independent or auto-regressive). For all MRT analyses, the (lagged) outcome of interest (eg, adherence to expenditure limit at Time_t+1_) will be regressed on a variable denoting the treatment received (ie, intervention vs control) at Time_t_, as well as covariates (including unbalanced time). The primary analyses will explore the effect of intervention versus control on the probability of adherence to expenditure limits in the subsequent episode. The identification of the conditions under which the interventions are most beneficial and how the effect of the interventions changes over the course of the MRT will be examined by specifying interaction terms between the intervention variable and interaction variables of interest (eg, strength of intention and time).

The long-term outcomes of the intervention (within-group follow-up evaluation) will be explored, whereby distal outcomes will be assessed using generalized estimating equations by regressing the outcome of interest (eg, gambling expenditure) on a variable denoting time (ie, before intervention, after intervention, and 6-month follow-up) and covariates. The identification of factors predicting longer-term outcomes will also be assessed by regressing the outcome of interest (eg, clinically significant changes in gambling expenditure) with selected preintervention, postintervention, and app usage variables. Where appropriate, missingness will be addressed using multiple imputations with appropriate accounting for the multilevel nature of the data (eg, multilevel multiple imputation).

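### One section makes follow-up of participants who lapse from EMAs conditional on engagement and another does not; the conditional rule selects the uncontrolled within-group sample on post-enrolment behaviour

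*Protocol article*

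**What the plan says.** Decision Points (protocol article) sets out reminders for people who do not complete onboarding or EMAs: an email, then a telephone call with an SMS or second email as back-up. It then states: "Participants who fail to complete an EMA following this protocol will receive no further contact". The same sentence keeps such people in the follow-up surveys on three conditions: they are "eligible to receive follow-up evaluations, as long as they complete onboarding, at least one EMA, and have some engagement with the app interventions". The text shown does not define how much engagement is enough.

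Within-Group Evaluation describes the posttreatment and 6-month surveys differently. On the invitation it says: "An email will be sent to all participants to prompt survey completion". On 6-month contact it says: "Participants who do not complete posttreatment evaluation will be contacted at the 6-month evaluation unless they have withdrawn from the study". Neither sentence mentions engagement.

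That component aims to "examine within-group change over the 6 months following the end of the MRT". Its primary outcome, gambling expenditure, comes from a calendar measure before intervention, from "the EMA data collected during the intervention period and amalgamated for the posttreatment evaluation", and from single items at 6 months. On missing data, Statistical Analyses says: "Where appropriate, missingness will be addressed using multiple imputations".

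**The concern.** A participant who onboards, completes a few EMAs, stops, never engages with an intervention and does not withdraw is treated differently by the two sections. Decision Points does not follow that person up. Within-Group Evaluation emails them after treatment and contacts them again at 6 months. With the engagement criterion undefined, staff would have to decide case by case.

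The Decision Points rule selects on what people did after enrolment. Interventions are offered only after a completed EMA crosses a threshold (Decision Rules; Microrandomization Procedure). The rule can therefore remove people who rejected the app and also people who lapsed before they were offered anything. The within-group evaluation has no control group, so randomization does not protect it against this selection. The Discussion nevertheless relies on it to determine whether expenditure, the primary distal outcome, falls. Acceptability is also measured partly by postintervention survey, and ratings from engaged participants only may look better than ratings from everyone.

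Outcomes not requested at these time points cannot be recovered by analysis later.

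**Working it through.** **1. The plan's own figures.** Inputs from Sample Size: 200 recruited, 40% attrition, availability 0.3, randomization probability 0.50, outcome probability 0.25 without intervention, relative risk 1.20, α = 0.05 (two-sided assumed). Decision points: 3 × 28 = 84 per person.

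- Retained: 200 × (1 − 0.40) = 120, as stated.
- Available decision points: 120 × 84 × 0.3 = 3,024, or 1,512 per condition.
- Comparing 0.25 with 0.25 × 1.20 = 0.30, observations taken as independent: power 0.869 (two proportions), 0.867 (log relative risk) or 0.861 (F version). All agree with the stated >85%.

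These figures concern the 28-day microrandomized comparison. Its outcomes come from EMAs, so who is sent a survey does not alter them.

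**2. The two rules for a lapsed participant who has not withdrawn.**

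| Case | Decision Points | Within-Group Evaluation |
|---|---|---|
| Onboarded, ≥1 EMA, engaged | Followed up | Followed up |
| Onboarded, ≥1 EMA, not engaged | Not followed up | Followed up |
| Onboarded, no EMA | Not followed up | Followed up |

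The last two rows conflict. The onboarding condition itself does little harm: the preintervention survey is part of the start-up sequence (Onboarding Procedure), and no change can be calculated without it.

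**3. What is lost.** Posttreatment expenditure comes from EMAs, so anything these participants recorded is kept, though it may be little because they stopped. The 6-month expenditure items and the survey-based secondary and acceptability outcomes are never requested.

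**4. Illustrative size.** Let f be the excluded share and r the mean change in the excluded divided by that in the followed group. Then

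full-cohort change ÷ followed-group change = (1 − f) + f·r

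overstatement = 1 / [(1 − f) + f·r] − 1

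Both f and r are assumptions; the article gives neither.

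| f | r = 0 | r = 0.5 | r = 1 | r = 1.25 |
|---|---|---|---|---|
| 10% | +11.1% | +5.3% | 0 | −2.4% |
| 20% | +25.0% | +11.1% | 0 | −4.8% |
| 30% | +42.9% | +17.6% | 0 | −7.0% |

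Example: f = 0.30, r = 0.5 gives 1/0.85 − 1 = 17.6%.

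**5. Could people lapse before being offered anything?** If the availability of 0.3 is read as the chance of intervention eligibility per completed EMA, independent between EMAs (an assumption), the chance of no offer is 0.7 after 1 EMA, 0.7³ = 0.34 after 3 and 0.7⁶ = 0.12 after 6. For early lapsers the route is real; for people who keep responding it soon becomes unlikely.

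**The case against.** *The sections can be read together.* Decision Points would define who is in follow-up, and Within-Group Evaluation would describe reminders for that group. This softens the sentence about emailing all participants. It fits less well with the sentence on 6-month contact, where withdrawal is the only exception. Even if accepted, it leaves the selection rule in force.

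*The excluded group may be small.* This is fair. The thresholds are broad (a score of 2 out of 5 on a high-risk item is enough), and choosing a strategy name in the control condition might count as engagement. These people had also ignored earlier reminders, so some would not answer if invited. How much the rule adds to ordinary non-response is unknown.

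*Imputation is planned.* It helps only in part. Lapsed non-engagers are never approached, so their values would be extrapolated from people who behaved differently, and the assumption could not be checked.

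*The component is supplementary.* It is, and a result restricted to people with some exposure could be reported as a narrower estimand. The article does not describe it that way.

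Two stronger inferences are not supported. A reader might conclude that the excluded have no outcome at all, but their EMA expenditure still feeds the posttreatment value. A reader might also conclude that the rule cuts off the range of app use to be studied as a predictor. The aim is to "identify predictors of these longer-term treatment outcomes (including usage of the app over the follow-up period", and someone with minimal engagement in the first 28 days who never opens the app again stays eligible. Only the zero or near-zero end of use during the 28 days is thinned.

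**Conclusion.** The concern holds in a limited form. The two sections give different instructions for lapsed participants who have not engaged, and the conditional rule introduces avoidable selection into an uncontrolled before-after evaluation of the primary distal outcome.

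A reader might take bias toward benefit as established. It is the usual expectation, but the documents do not show it. Early lapsers who were never offered an intervention could shift the estimate either way. The upper figures of 11% to 43% require that the excluded did not change at all, which is not a neutral assumption for help-seekers. The whole illustration also assumes that the excluded would respond if invited.

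The effect falls on 6-month expenditure and the survey-based outcomes, less on posttreatment expenditure. The microrandomized comparison, the 200 and 120, and the >85% power all stand. The point should be dealt with because the lost data cannot be recovered and the remedy is cheap; it does not threaten the trial's main randomized result.

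**What to change.** In Decision Points, drop the engagement condition and the one-EMA condition. The second must go too, because during the 28 days nobody reaches an intervention without completing an EMA. State that everyone with preintervention survey data is invited to both follow-ups unless they have withdrawn, and align Within-Group Evaluation. Make that set the main within-group analysis. Use engagement, with a stated definition, only as a predictor or in a sensitivity analysis.

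Recruitment had begun when the article was written. If the rule has already been applied, report how many people were not approached and their baseline characteristics, and repeat the 6-month analysis under a range of assumed changes for them.

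Cost: Aus $50 for each of two evaluations, so up to Aus $100 in vouchers per additional responder, plus reminder emails, up to two researcher calls per non-responder and a short amendment. No stated sample size or power figure changes.

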### Tailoring Variables

The eligibility for EMI content is guided by a set of tailoring variables and decision rules [43,45,60-62]. In this study, all 18 EMA items serve as tailoring variables to ensure *Gambling Habit Hacker* delivers the right amount of support at the right time. The choice of tailoring variables is aligned with the HAPA model in terms of strengthening goal intention and addressing internal or situational variables that could weaken intention and the ability to implement and maintain behavioral attention. Gamblers report that motivation is a major barrier to adhering to gambling expenditure limits and that internal and situational factors make it challenging to maintain change [63]. Tailoring variables targeting both the motivation (strength of intention for goal adherence) and volition (being able to implement and maintain actions to limit gambling) phases were selected.

Tailoring variables are presented in Multimedia Appendix 1 [64-66]. The first set of tailoring variables was the strength of intention (*Right now, I intend to meet my goal*) and goal self-efficacy. (*Right now, I am confident that I can stick to my goal*). These variables relate to the proximal outcome of adhering to gambling expenditure limits and were adapted from the study by Schwarzer et al [64]. The second tailoring variable was designed to support urge self-efficacy and focused on the confidence to adhere to gambling limits despite an urge to gamble (*Right now, it would be difficult to turn down a bet*). This variable is measured using a single item from the Gambling Urge Scale [65]. The third set of tailoring variables supports maintenance of self-efficacy (confidence in implementing an action). To do this, the focus is on high-risk situations, which are internal and situational variables that are well-established barriers to adhering to gambling expenditure limits [63]. Participants are asked to indicate whether they were currently experiencing negative reinforcement high-risk situations (*difficulties and conflict or arguments with other people*), positive reinforcement high-risk situations (*thinking that my skill or system could help me to win at gambling*), consuming alcohol or drugs, and gambling proximity (*gambling right now as planned*). Positive and negative reinforcement high-risk situations were drawn from the study by Smith et al [66], with the addition of a single item assessing current physical discomfort (*physically uncomfortable or trouble sleeping*). Alcohol and drug consumption and gambling proximity were single items developed for this study. High-risk situations are assessed on a 5-point Likert scale from 1=*not at all* to 5=*completely*.

### Decision Rules

*Gambling Habit Hacker* determines eligibility for an intervention based on responses to the 18 tailoring variables. A threshold was set for each tailoring variable, which was used to determine whether the person was eligible for an EMI. As shown in Multimedia Appendix 1, the thresholds varied across each tailoring variable. A score of 1 to 3 (strongly disagree to neutral) was the threshold for the strength of intention (to adhere to gambling expenditure limits) and goal self-efficacy. A score of 3 to 5 (neutral to strongly agree) was the threshold for urge self-efficacy. A score of 2 to 5 was the threshold for being in a high-risk situation.

Each strategy group is linked to at least one tailoring variable, whereby 14 strategy groups were identified for strengthening intention to adhere to gambling limits, 12 strategy groups for goal self-efficacy, 16 strategies for urge self-efficacy, and all 25 strategy groups for high-risk situations. As shown in Table 1, each high-risk situation was allocated between 2 and 9 different strategies that could be used to directly address potential risk to adhering to gambling expenditure limits. Some strategies were specific to only 1 or 2 tailoring variables; for example, the strategy *slow down the bets* is only relevant to gambling on an intended gambling day. Other strategy groups, such as *talk to someone*, *seek professional support*, and *improve motivation*, are offered across almost all situations.

If participants reach EMI eligibility on several tailoring variables, a predetermined hierarchy (achieved through researcher consensus) is implemented, in which the app will deliver the EMI relevant for the highest ranked EMA item. The following hierarchy was determined, ranging from the most to least immediate threat to adhering to gambling expenditure limits: gambling proximity (whether the person is currently engaged in planned or unplanned gambling or whether it is a planned gambling day), weakened urge self-efficacy, being in a high-risk situation, weakened strength of intention to adhere to limits, and weakened goal self-efficacy. We consider current gambling to be the most serious high-risk situation for adhering to gambling expenditure limits, whether planned or unplanned.

Importantly, a *provide nothing* option is provided for situations in which the participant ignores the push notification prompting EMA completion or presses the *snooze* function to indicate that they are currently unable to complete the EMA (which suggests that they are not in a state of receptivity).

**Table 1 table1:** Just-In-Time Adaptive Intervention decision rules linking tailoring variable (time-based ecological momentary assessment) with ecological momentary intervention response^a^.

Strength of intention	Goal self-efficacy	Urge self-efficacy	High-risk situations^b^	EMI strategy group activated^c^
✓	✓	✓	Q1, Q4, Q5, Q6, Q7, Q11, and Q14	Build commitment
✓	✓		Q3 and Q8	Build momentum
✓			Q6, Q9, Q10, Q13, and Q14	Control cash in venue
✓	✓	✓	Q1, Q4, Q6, Q8, Q9, Q10, Q12, Q13, and Q14	Control gambling urges
✓	✓	✓	Q1, Q2, Q3, Q4, Q5, Q6, Q7, Q9, Q11, and Q14	Do something else
✓		✓	Q1, Q3, Q4, Q5, Q6, Q11, and Q14	Deal with emotions
		✓	Q2, Q3, Q5, Q7, Q8, Q11, and Q13	Grab a treat
✓		✓	Q3 and Q12	Impose rewards and consequences
	✓		Q8 and Q12	Keep to budget
✓		✓	Q1, Q3, Q6, Q8, Q12, and Q14	Know reasons for change
✓	✓		Q4, Q9, Q12, Q13, Q14, and Q15	Know tricks pokies play
			Q4, Q13, Q14, and Q15	Know when to walk away
	✓	✓	Q1, Q4, Q7, Q8, Q10, Q13, Q14, and Q15	Limit cash
	✓	✓	Q6, Q7, Q8, Q10, Q13, and Q15	Prepokies prep
		✓	Q1, Q4, Q5, Q8, Q9, Q10, Q12, Q13, and Q14	Reduce cash in hand
✓	✓	✓	Q1, Q4, Q5, Q6, Q7, Q9, and Q10	Reduce gambling thoughts
			Q2, Q8, Q10, and Q11	Reduce stress
✓	✓	✓	Q1, Q2, Q4, Q6, Q8, Q13, Q14, and Q15	Strengthen goal
✓			Q3, Q10, Q11, and Q12	Support good health
✓	✓	✓	Q1, Q2, Q3, Q8, Q9, Q10, Q11, Q13, and Q14	Seek professional support
			Q4, Q9, Q13, Q14, and Q15	Self-control in the venue
			Q9 and Q13	Slow down the bets
		✓	Q1, Q4, Q5, Q6, Q7, Q9, Q10, and Q12	Stay away from venues
		✓	Q5, Q6, Q7, and Q11	Swap gambling
✓	✓	✓	Q1, Q2, Q3, Q5, Q6, Q7, and Q14	Talk to someone

^a^On the basis of whether the participant has the current availability to complete the ecological momentary assessment.

^b^Q1: temptations to gamble, such as having money or being reminded of gambling; Q2: difficulties, conflict, or arguments with other people; Q3: unpleasant feelings such as depression, loneliness, or frustration; Q4: wanting to win back money or thinking about winning more; Q5: feeling good and want to gamble today, but today is a no gamble day; Q6: people are encouraging, pressuring, or creating a desire to gamble; Q7: wanting to pass some time; Q8: worry about debt or how you will pay the bills; Q9: thinking that your skill or system could help you to win at gambling; Q10: you are drinking or taking drugs; Q11: physically uncomfortable or having trouble sleeping; Q12: beginning to think that you no longer have a gambling problem; Q13: gambling right now as planned; Q14: gambling right now but not planned; Q15: not gambling right now but a planned gambling day.

^c^Refer to Table 2 for strategies within each group.

